#### **9-5 Concomitant medication**

Not applicable.

### **10 REGULATORY AND ETHICAL ASPECTS**

#### **10.1. Study conduct and sponsor responsibilities (COL)**

The study must be conducted in accordance with the ethical principles of the Declaration of Helsinki, Good Clinical Practice (GCP) of the International Conference of Harmonization (ICH-E6), Law 2004-800 of 06AUG2004 on bioethics and the provisions of the Public Health Act of 09AUG2004 and the implementing decree of 26APR2006.

The sponsor must ensure essential documents on the conduct of the study are stored under conditions ensuring their safety, for the minimum duration provided by GCP, i.e., 15 years after the end of the research.

#### **10.2. Study conduct and investigator responsibilities**

The principal investigator at each institution undertakes to conduct the clinical trial in accordance with the protocol that has been approved by the EC and ANSM. The investigator cannot deliberately carry out a protocol deviation without the authorization of the EC and the ANSM.

It is the responsibility of the principal investigator:

- to provide the sponsor with his/her *curriculum vitae* as well as those of the co-investigators,
- to identify the members of his/her team participating in the trial and to define their responsibilities,
- to start recruiting patients after authorization from the sponsor,
- to make every effort to enroll the required number of patients within the established recruitment period.

It is the responsibility of each investigator:

- to collect the informed consent personally signed and dated by the patient before any trial-specific screening procedure,

- to regularly complete the case report forms (eCRFs) for each patient enrolled in the trial and to allow the Clinical Research Associate Monitor (CRA-M) direct access to the source documents so that the latter can validate the CRF data,
- to date, correct and validate the eCRF corrections for each patient enrolled in the study,
- to accept the regular visits of the CRA monitor, and possibly those of auditors mandated by the sponsor or inspectors of the supervisory authorities.

All documentation relating to the study (protocol, consents, CRF, investigator file, etc.), as well as the original documents (laboratory results, radiology, consultation reports, clinical examination reports prepared, etc.) must be kept in a secure location and considered confidential material.

The archiving of data will be under the responsibility of the investigator and according to current legislation. The investigator will keep the data and a patient identification list for a minimum of 15 years after the end of the study.

### 10.3. Ethics Committee (EC)

In accordance with the applicable regulations, the clinical study protocol and the various amendments are submitted by the study sponsor for the opinion of an EC.

### 10.4. Participant information and consent

Prior to the conduct of biomedical research on a subject, the **free, informed consent** of the subject must be collected after he/she has been informed of the purpose of the research, the conduct and duration of the study, the potential benefits, risks and constraints of the study, and the opinion given by the EC and ANSM.

The consent form will be personally signed and dated by the patient and the investigator (original filed by the investigator, a copy will be given to the patient).

### 10.5. Patient Committee

The protocol will be reviewed by the Patient Committee of the National League Against Cancer (*Ligue Nationale Contre le Cancer*, LNCC) particularly focusing on the quality of the information letter, provision of a treatment and monitoring plan and the suggestion of measures to improve patient comfort.

### 10.6. Independent Monitoring Committee

The establishment of an independent trial monitoring committee will be set up to ensure the protection of patients, to ensure that the trial is conducted ethically, to assess the risk-benefit ratio of the trial and to ensure the review of the scientific findings during and at the end of the trial. The Monitoring

Committee will meet mid-study and then, if applicable, in case of high incidence of pelvic cancers, during the monitoring period of patients.

It will consist of 3 members:

- 1 biostatistician: **[name]**, Léon Bérard Center, Lyon
- 1 surgeon: **[name] [name]**, Gustave Roussy Institute, Villejuif
- 1 oncogenesis specialist: **[name]**, Jeanne de Flandre Hospital, Lille CHRU (*Centre hospitalier régional universitaire* [Regional University Hospital])

## 10.7. Confidentiality

In accordance with the French Public Health Code, the investigators and all persons called to collaborate in the study are required to maintain confidentiality with respect to the study, the participants and the findings obtained. The investigator must ensure that the anonymity of patients is respected. The investigator maintains a confidential patient identification list.

## 11 OPERATIONAL MANAGEMENT OF THE STUDY

### 11.1 Study organization

This study is sponsored by the Hauts-de-France Cancer Center: the Oscar LAMBRET Center of Lille (COL).

### 11.2. Cost and additional cost of the research

Any additional costs related to activities that are not routinely performed are the subject of an agreement negotiated between the COL and the investigator site representative, taking into account the financial resources available to the COL as part of its public promotion activity.

However, the COL ensures the organization and logistics (protocol, electronic case report form, investigator file) necessary for the conduct of the study.

### 11.3. Monitoring

Initiation visits or telephone meetings, follow-up visits, and close-out visits or letters are carried out by the CRA monitor appointed by the sponsor, in accordance with GCP.

### 11.4. Quality assurance

The Sponsor is responsible for the implementation and maintenance of a quality assurance system to ensure that the study is conducted in accordance with the protocol and GCP.

### 11.5. Ownership of data and publication

At the end of the study, a report will be written by the sponsor and then validated by the coordinator. No publication or presentation of the results of this trial may be made without the sponsor's consent.

Any publication shall at a minimum refer to:

- the coordinating investigator,

- all those who have participated in the study. The order of co-authors will take into account the participation of the various investigators in the trial (number of patients enrolled and assessable).
- all those who have contributed significantly to the conduct of the study and the publication process: the CRA monitor, the project manager, the biostatistician, the head of the Clinical Research and Innovation Department, and the sponsor.

Furthermore, any publication will include thanks to:

- Participating site research technicians,
- INCa (PHRC 2011),
- Study related partners (CTD-CNO)

The sponsor's review and agreement are required before any communication.

## 13- APPENDICES

### ***Appendix 1 – Study schedule***

| EXAMINATIONS                                        | Prior to enrollment
and within 28 days
prior to
fimbriectomy | 30 days after
fimbriectomy | Once a
year | Withdraw
al from
the study
(3) |
|------------------------------------------------------------|---------------------------------------------------------------------------------|---------------------------------------|------------------------|---------------------------------------------------|
| Consent signature                                          | X                                                                        |                                       |                        |                                                   |
| Inclusion criteria                                         | X                                                                        |                                       |                        |                                                   |
| Exclusion criteria                                         | X                                                                        |                                       |                        |                                                   |
| PHYSICAL EXAMINATION                         | X                                                                        | X                              | X               | X                                          |
| Gynecological examination                                  |                                                                                 |                                       |                        |                                                   |
| Anesthetic evaluation of surgical non-
contraindication | X                                                                        |                                       |                        |                                                   |
| Postoperative Complications                                |                                                                                 | X                              |                        |                                                   |
| LABORATORY TESTS                             | X                                                                        |                                       | X (1)           | X (1)                                      |
| • FSH, Estradiol                                           |                                                                                 |                                       |                        |                                                   |
| • LH                                                       |                                                                                 |                                       |                        | X                                          |
| • Inhibin B                                                |                                                                                 |                                       |                        |                                                   |
| • Anti-Müllerian Hormone (ovarian
reserve)              | X                                                                        |                                       | X (1)           | X (1)                                      |
| • CA-125                                                   | X                                                                        |                                       | X               | X                                          |
| • βHCG                                                     | X (within 7 days
before surgery)                                     |                                       |                        |                                                   |
| PARACLINICAL EXAMINATIONS                    |                                                                                 |                                       |                        |                                                   |
| • Endovaginal and supravaginal
ultrasound               |                                                                                 |                                       | X (2)           | X (2)                                      |
| • +/- Pelvic MRI                                           |                                                                                 |                                       |                        |                                                   |

(1) If you have menstrual problems or symptoms of menopause

(2) Transvaginal and supravaginal ultrasound in case of increased marker confirmed by a second sample +/- pelvic MRI in case of clinical signs

(3) See chapter 8.6.4

## **Appendix 2 – Letter to non-hospital gynecologists**

Doctor .....

On ...

**Subject:** *FIMBRIECTOMIE-1106 clinical study*

**Patient's last name and first name:** .....

**Date of birth:** [ ]-[ ]-[ ] [ ]-[ ]-[ ] [ ]-[ ]-[ ]-[ ]

**Patient's initials:** [ ]-[ ] **Patient Number:** [ ]-[ ]-[ ]-[ ]

Dear Colleague,

We are currently participating in a clinical study sponsored by the Oscar Lambret Center entitled ***Radical fimbriectomy for young women at hereditary risk of serous pelvic cancer*** (FIMBRIECTOMIE-1106). This is a study in which the above-named patient agreed to participate and underwent a fimbriectomy on .....

The rationale for this study is based on the increased risk of women with deleterious BRCA1/2 mutations developing breast or ovarian cancer, often reluctant to undergo adnexal surgery. The pelvic risk is even greater in women who have previously had breast cancer. Based on data from the literature, pathology findings reveal that most occult precancerous lesions occur not on the ovary but on the tube and especially on the fimbrial end of the fallopian tube. Its objective is to assess the incidence of pelvic serous cancer after prophylactic radical fimbriectomy in women at hereditary risk of pelvic serous cancer, but not ready for prophylactic adnexectomy. This trial also aims to determine the occult lesion rate on the fimbriectomy specimen, the incidence or recurrence of breast cancers, the rate of secondary oophorectomy and [its] morbidity, and postoperative complications.

In this study, patients should receive annual monitoring until menopause (breast-gynecological examination). Any menopausal symptoms or menstrual disturbances should trigger routine laboratory tests as per the study protocol (FSH, estradiol, inhibin B, AMH, and CA-125).

This is why we would be grateful if you could let us know:

- of any adverse event that could occur in this patient: signs and symptoms that may be reasonably related to surgery, menstrual disorders, hot flashes, vaginal dryness, etc.,
- the occurrence of pelvic cancer, breast cancer,
- and any additional pelvic surgery procedure.

If you have any questions or would like more information, please contact the investigator site in charge of monitoring this patient (see contact details below).

Thank you for your help. Sincerely,

Name, date and signature

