| PHYSICAL EXAMINATION
Gynecological examination
Additional examination left to clinician discretion  | Once a year                                                        |
| LABORATORY TESTS
- FSH, estradiol, inhibin B and anti-Müllerian hormone (ovarian reserve)              | In case of menstrual disorders or menopausal symptoms              |
| - Annual CA-125                                                                                                  | Once a year                                                        |
| PARACLINICAL EXAMINATIONS
- Transvaginal and suprapubic ultrasound
- ± pelvic MRI if clinical signs | Pelvic ultrasound, if marker increase confirmed by a second sample |
| QUESTIONNAIRE
- Satisfaction questionnaire                                                             | Once during follow-up                                              |

The investigator must inform the non-hospital gynecologist of the patient's participation in the trial, and the need to investigate, at each consultation:

- any adverse event that may reasonably be related to surgery, such as menstrual disorders, hot flashes, vaginal dryness, etc., until the onset of menopause;
- any signs suggestive of pelvic cancer, breast cancer, or its recurrence;
- and any additional pelvic surgery procedure

A letter for non-hospital gynecologists is provided for this purpose (Appendix 2).

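### The Appendix 2 letter to outside gynecologists leaves out the annual CA-125, ties CA-125 to symptoms, and does not ask for breast cancer recurrence to be reported

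*Protocol*

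**What the plan says.** **The letter (Protocol, Appendix 2).**
- Yearly monitoring: "In this study, patients should receive annual monitoring until menopause (breast-gynecological examination". No laboratory test is attached to it.
- CA-125 appears once, in a panel that depends on symptoms: "Any menopausal symptoms or menstrual disturbances should trigger routine laboratory tests as per the study protocol (FSH, estradiol, inhibin B, AMH, and CA-125".
- The list of events to report gives, for cancers, "the occurrence of pelvic cancer, breast cancer". Recurrence is named earlier in the letter, where the trial's aims are described: "the incidence or recurrence of breast cancers".
- For questions, the letter directs the reader elsewhere: "please contact the investigator site in charge of monitoring this patient".

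**The protocol body.**
- The follow-up table in section 8-6-3 gives CA-125 its own row, timed once a year and with no condition. A separate row holds "FSH, estradiol, inhibin B and anti-Müllerian hormone (ovarian reserve", timed "In case of menstrual disorders or menopausal symptoms".
- Section 8-6-3 also requires the investigator to tell the outside gynecologist of the patient's "participation in the trial, and the need to investigate, at each consultation", three things: adverse events that may be related to the surgery; signs of pelvic cancer, of breast cancer or of breast cancer recurrence; and further pelvic surgery. It says the Appendix 2 letter is provided for that purpose.
- Recurrence of breast cancer is part of a secondary objective (section 7-2) and of the endpoint in section 8-7-3.

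**The concern.** The letter tells a doctor outside the trial which tests are due and which events to send back, and it cites the protocol as its authority. Where it departs from the protocol, a doctor who follows it faithfully will depart from the protocol too.

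Two things are at stake. First, a woman without symptoms is due a yearly CA-125 that the letter never mentions. In section 8-6-3 a confirmed rise in the marker is what leads to pelvic ultrasound, so an assay that is not done also removes that trigger. Second, a recurrence seen outside the site may not be reported, and it counts as an event for the breast endpoint. Section 6-2 expects that a substantial share of the women enrolled will already have had breast cancer, and these are the women in whom a recurrence can occur. Under-reporting would bias that cumulative incidence downward.

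**Working it through.** There is no figure in the plan to reproduce. The check sets the letter beside the sections it should match.

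| Item | Section 8-6-3 | Appendix 2 letter |
|---|---|---|
| Due every year, no condition | gynecological examination; CA-125 | examination only |
| Triggered by menstrual or menopausal symptoms | FSH, estradiol, inhibin B, AMH | the same four, plus CA-125 |
| Cancer events | pelvic cancer; breast cancer; breast cancer recurrence | pelvic cancer; breast cancer |

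**Counts.**
- Unconditional yearly items: 2 in section 8-6-3, of which the letter states 1.
- Symptom-triggered assays: 4 in section 8-6-3; the letter lists 4 + 1 = 5, and CA-125 is the extra one.
- Cancer events: 3 in section 8-6-3, of which 2 are on the letter's reporting list.

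**Is section 8-6-3 itself the slip?** No. In Appendix 1 the yearly mark for CA-125 carries no footnote, while the hormone tests carry footnote 1, the symptom condition. Section 8-6-4 makes the same split at study withdrawal: hormones conditional, CA-125 a separate single assay. Three places in the protocol agree with each other, and the letter stands alone.

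**Which women are meant?** Section 8-6-3 applies its monitoring scheme to women without lesions on the specimen. Women with invasive cancer or STIC on the specimen meet the early withdrawal criterion in section 8-4. The yearly CA-125 therefore applies to the women still in follow-up, the same women whose monitoring until menopause the letter describes.

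**Was recurrence left out on purpose?** Nothing suggests so. Of the three things section 8-6-3 wants conveyed, adverse events and further pelvic surgery reach the letter's list in full. Only the cancer item is shortened. Both the protocol and the letter's own paragraph on aims name recurrence alongside new breast cancer.

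**Upper bound on the women concerned.** The synopsis gives 123 enrolled, so the number is at most 123, less those not operated on or already withdrawn. The documents do not say how many women have assays or event reports handled outside the site. The bound therefore cannot be turned into an expected number of missed assays or missed events.

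**The case against.** The best reply is that the letter's stated purpose covers only the three things to be investigated and reported. That list contains no laboratory schedule, and no section says that outside gynecologists order the yearly marker. The site's duty under section 8-6-3 is untouched, and the letter itself describes the site as in charge of monitoring. The letter also does not forbid a yearly CA-125, and an additional assay in a woman with symptoms does no harm. On recurrence, the letter names it among the aims, so a careful reader may take breast cancer to include it. The yearly visit and the case report form give another route for these data. Finally, section 8-6-3 says that surveillance has not worked as screening for high-grade serous carcinoma, so little may be lost for the primary endpoint.

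Most of this stands, and it is why the point is minor. It does not remove the mismatch. Once the letter tells outside doctors which tests are due and attributes that to the protocol, the statement should be right, even if section 8-6-3 did not require the letter to carry a laboratory schedule. The omission of recurrence falls squarely within the letter's stated purpose, so it is the firmer of the two faults. The remark on surveillance is followed in the same section by the view that it makes more sense for type 1 and non-epithelial tumors, and the section still prescribes the yearly CA-125.

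**Conclusion.** The concern holds as a minor one. The letter is an incomplete summary of follow-up: it attributes a symptom-triggered CA-125 to the protocol and is silent on the yearly one. It also asks for fewer cancer events than section 8-6-3 requires and section 8-7-3 counts.

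Any effect falls mainly on ascertainment of breast cancer recurrence, a secondary endpoint, and on adherence to the yearly marker where outside care follows the letter. How far that happens is not documented, so no effect on an endpoint can be sized. None on the primary endpoint is shown. The population, schedule, endpoints and analysis in the protocol body are not in question.

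**What to change.** Correct two items in Appendix 2:

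1. **Monitoring.** State that every woman in follow-up is due a breast and gynecological examination and a CA-125 each year until menopause. Limit the tests triggered by menopausal symptoms or menstrual disturbance to FSH, estradiol, inhibin B and AMH.
2. **Reporting.** Ask for any pelvic cancer, any new breast cancer and any recurrence of breast cancer.

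Send the corrected letter to the outside gynecologists of women still in follow-up. Recruitment ended in October 2014, so changing the template alone would reach nobody who already holds the old letter. The study is projected to run to August 2034, so a correction can still be of use.

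The cost is two wording changes and one mailing. Assuming one gynecologist per woman, that is 123 × 1 = 123 letters at most, and fewer after withdrawals. Nothing changes in the design, sample size, procedures or analysis.

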### **Appendix 3 – 2009 Clavien-Dindo classification of surgical complications**

This classification is used for surgical complications that occur up to 30 days after surgery.

| Grades     | Definition                                                                                                                                                                                                                                                                                                                                   |
|-------------------|-----------------------------------------------------------------------------------------------------------------------------------------------------------------------------------------------------------------------------------------------------------------------------------------------------------------------------------------------------|
| I          | Any deviation/divergence from normal postoperative follow-up not requiring pharmacological or surgical treatment, or endoscopic or radiological intervention
Allowable treatments are: drugs such as antiemetics, antipyretics, analgesics, diuretics, as well as electrolytes and physiotherapy.
This grade also includes infected injuries. |
| II         | Requiring pharmacological treatment with drugs other than those authorized for grade I complications
Transfusions and parenteral nutrition are also included in this grade.                                                                                                                                                                      |
| III        | Requiring a surgical procedure, endoscopic or radiological                                                                                                                                                                                                                                                                                          |
| III-a             | Without general anesthesia                                                                                                                                                                                                                                                                                                                          |
| III-b             | With general anesthesia                                                                                                                                                                                                                                                                                                                             |
| IV         | Life-threatening complication (including central nervous system complications) whether or not requiring hospitalization in intensive care                                                                                                                                                                                                           |
| IV-a              | Single organ dysfunction (including dialysis)                                                                                                                                                                                                                                                                                                       |
| IV-b              | Multiple organ dysfunction                                                                                                                                                                                                                                                                                                                          |
| V          | Patient death                                                                                                                                                                                                                                                                                                                                       |
| "d" suffix | If the patient has a complication at the time of discharge, "d" suffix (for "disability") is added to the respective grade of the complication. This label indicates the need to track the event in order to assess the complication fully.                                                                                                         |

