### ***8-7-5 Postoperative complications***

Morbidity will be assessed:

- up to 30 days post-procedure according to the Clavien-Dindo classification [2009]
- and beyond this time (until confirmation of menopause for patients who have not had a secondary oophorectomy, or up to one month after secondary oophorectomy) according to the NCI-CTCAE v4.0 grading scale.

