Early postoperative morbidity (assessed by Clavien-Dindo scale within 30 days post-operatively) and late postoperative morbidity (occurring in a period of more than 30 days and assessed by NCI-CTCAE) will be described by type of adverse event, grade and relationship to the fimbriectomy or secondary oophorectomy. The type of adverse event (AE) will be described by SOC (System Organ Class) and PTname (Preferred Term) of the medDRA medical dictionary. The maximum grades observed by type of AE will be described in tabular form: number and frequency. Serious adverse events (SAE) will be described.

Each item of the satisfaction questionnaire will be described by its median, extreme values, mean and standard deviation.

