| Urine                 | 

• Bladder wound

• Ureteral wound

                                                     | 

• Fistula

• Stenosis

• Bladder disorders (2)

                                                                                                                       |
| Infectious            |                                                                                                                                              | 

• Urinary tract infection

• Abscess

• Secondary infection (abscess, lymphocele)

• Sepsis at surgical site or not

                                           |
| Neurological          | 

• Nerve wound (obturator, femoral, genitofemoral nerve involvement)

• Ureteral wound

 | 

• Obturating femoral cutaneous neuralgia

• Paresthesia, lower extremity dysesthesia

• Lower extremity mobility disorder (adduction disorder)

                       |
| Other                 | 

• Anaphylactic shock

• Quincke's edema

                                               | 

• Anaphylactic shock

• Umbilical hernia

• Eventration, complicated or not

• Pain (abdominopelvic)

• Fatigue, heaviness, weight

• Menopause

 |

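### Appendix 3 puts infected wounds in Grade I without limit, so one treated with a drug outside the Grade I list can be read as Grade I or Grade II

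*Protocol*

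**What the plan says.** Protocol section 8-7-5 measures morbidity in the first 30 days by the Clavien-Dindo classification of 2009 and uses NCI-CTCAE v4.0 after that. Appendix 3 reproduces the early scale and states its window: "This classification is used for surgical complications that occur up to 30 days after surgery".

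The Appendix 3 rows that matter here are:

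- **Grade I, definition:** "Any deviation/divergence from normal postoperative follow-up not requiring pharmacological or surgical treatment, or endoscopic or radiological intervention".
- **Grade I, permitted treatment:** "Allowable treatments are: drugs such as antiemetics, antipyretics, analgesics, diuretics, as well as electrolytes and physiotherapy".
- **Grade I, addition:** "This grade also includes infected injuries".
- **Grade II:** "Requiring pharmacological treatment with drugs other than those authorized for grade I complications". A further line places transfusions and parenteral nutrition in this grade.
- **Grade III:** complications needing a surgical, endoscopic or radiological procedure, split into III-a and III-b by use of general anesthesia.

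Section 8-8-2 sets the reporting: "The maximum grades observed by type of AE will be described in tabular form: number and frequency". Section 8-7-5-1 requires each adverse event to be recorded with its nature, date of onset and associated treatments, among other items.

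**The concern.** The table is built on one principle: the treatment needed fixes the grade. The sentence on infected wounds assigns a grade by diagnosis instead and does not say how the two principles combine. An investigator with a drug-treated wound infection can defend either of two grades from the same page.

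Morbidity of the fimbriectomy is the first-listed secondary objective, and this is its only scale for the first 30 days. There are 14 sites. If some follow the sentence and others follow the treatment rows, the maximum-grade table mixes two conventions. Where the sentence is followed literally, the error runs one way: treated infections are counted in a lower grade than the treatment rows would give.

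**Working it through.** The protocol states no figure to reproduce. The check is a comparison of the rows of Appendix 3, followed by one line of arithmetic on size.

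**Step 1: what the added sentence can add.** The Grade I definition, with its permitted treatments, already covers any deviation that needs nothing beyond that list. An infected wound managed that way is Grade I without the extra sentence. The sentence therefore changes a grade only if it reaches infections treated beyond the list. The Grade II row claims the drug-treated ones among these.

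**Step 2: three cases.**

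| Infected wound that required | By the added sentence | By the treatment rows | Conflict |
|---|---|---|---|
| Nothing, or Grade I treatments only | I | I | None |
| A drug outside the Grade I list | I | II | Yes |
| A surgical, endoscopic or radiological procedure | I, if read without limit | III-a or III-b | Weaker |

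The third case is weaker because the grades are ordered. The Grade II row has a parallel line on transfusion, and nobody would hold a transfused patient at Grade II after a re-operation. The same habit of reading would move an infected wound up once it needed a procedure.

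**Step 3: does another section settle the second case?**

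- Section 8-8-2 takes the maximum over grades already assigned. It does not say which grade a single event receives.
- Section 8-7-5-5 gives a fallback scale based on daily activity, but only for events the classification does not list. Infected wounds are listed.
- Sections 8-7-5 and 8-7-5-1 fix the time window and the data to record. They give no rule of precedence between rows.

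**Step 4: size per event.** The planned maximum in section 8-8-1 is 120 patients. One wound moved between Grade I and Grade II or higher changes the proportion at Grade II or higher by 1/120 = 0.83 percentage points. The synopsis reports 123 enrolled, with three added to replace patients who could not be assessed, for example because they were not operated on. With 123 as denominator the change is 1/123 = 0.81 points, so the choice hardly matters.

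**Step 5: can sites still be guided?** The synopsis has recruitment ending in October 2014. Under section 8-6-1 the baseline assessment precedes enrollment and falls within 28 days before surgery. Taking 31 October as the latest enrollment, surgery falls by 28 November and the 30-day window ends by 28 December 2014, if the schedule was kept. Site grading under Appendix 3 is therefore finished on the protocol's own dates.

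**The case against.** The strongest reply is that the sentence sits inside the Grade I row and is governed by that row's first line. It would then cover only infected wounds managed within Grade I, and no conflict arises. This reading is possible and may be what was meant. It does not remove the point, because the text does not state it. On this reading the sentence is a clarification, while its wording, like the parallel Grade II line, reads as an assignment of a named condition to a grade. For infections needing a procedure, however, the ordered-scale argument largely succeeds.

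A second reply is that the Grade I drug list is given as examples, so an anti-infective might be allowed. None is named. An open list gives sites more room to differ over drug-treated infections.

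A third reply is that Appendix 3 reproduces a published scale in translation, and the sentence may be the source's own wording. That cannot be checked from the protocol. The fix should therefore include a comparison with the cited classification and should not presume an error of copying.

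A reader might also argue from Appendix 6, which lists "Sepsis at surgical site or not" among expected serious events, that a blanket Grade I is contradicted there. The protocol does not support this. Section 8-7-5-5 separates intensity from the criteria that drive reporting, and the same appendix lists nausea and constipation, so presence on that list says nothing about grade.

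**Conclusion.** The inconsistency is real but small. For infected wounds treated with a drug outside the Grade I list, Appendix 3 supports both Grade I and Grade II on a literal reading, and no rule of precedence is given. The overlap with Grade III is weaker.

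Each affected wound shifts the proportion at Grade II or higher by about 0.83 percentage points, assuming 120 operated patients. That proportion is used here only as a yardstick, since section 8-8-2 plans a table of maximum grades by event type and no such summary. The endpoint is secondary and descriptive, with no threshold attached. The primary endpoint, sample size and stopping rule are untouched.

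A reader might infer that harm has been understated by some known share, for example by applying the 3.1% postoperative complication rate in section 8-7-5-3 to this trial. That figure covers all postoperative complications in an adnexectomy series. It is neither an infection rate nor a rate at Grade II or higher. The protocol gives no basis for saying how many wounds are affected, or that any were in fact under-graded.

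**What to change.** Reconcile the infected-wound sentence in Appendix 3 with the Grade II and III rows, after comparing it with the classification that the protocol cites, and state which row prevails when an infection was treated beyond the Grade I list.

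Since rewording can no longer change how sites graded, apply the rule at the final analysis. Identify each wound infection recorded within 30 days of fimbriectomy and re-derive its grade from the associated treatments collected under section 8-7-5-1. Use the re-derived grade in the maximum-grade table and report how many grades changed.

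The cost is one clarifying sentence and a check of what should be a few records. No new data are needed. The morbidity figures may come out slightly less favourable.
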